# Adverse events

We anticipate only a very small number of adverse events (SAEs), but case definitions, standardised opportuning procedures and a reporting protocol will be in place, and any event deemed to be a serious adverse event will be reported to all IRBs within 7 days of reporting. Additionally, all SAEs will be reviewed by the DSMB.

Events deemed to be serious adverse events and systematically recorded and reported, and will include:

- Misclassification or misinterpretation of HIV or TB results leading to a participant starting treatment in error, or failing to start treating
- Adverse reaction to tuberculosis skin testing, such as ulceration, gangrene or loss of limb, disseminated infection, or death
- Participant withdrawal due to reported stigma, discrimination or breach in confidentiality
- Needlestick injuries to participants or staff
- Episodes of violence or discrimination reported by participants or other household members, or other parties, that is attributed to study contacts or interventions.

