2. HIV testing with prompt initiation of both antiretrovirals and TB preventive treatment for HIV-infected contacts according to current South African guidelines,
3. Preventive therapy for tuberculin skin test-positive, HIV-negative **and** HIV-infected household contacts without active TB disease;
4. A three-month supportive follow-up visit to confirm treatment receipt, and assist those who have either not accessed care and treatment; or who have experienced problems with their treatment; or who have developed symptoms of TB in the interim.

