In the intervening period since the final ZAMSTAR prevalence survey in 2010, there have been considerable advances in TB diagnosis, and prevention. Routine TB diagnostics have improved markedly with the widespread scale-up of the Xpert MTB/Rif molecular TB diagnostic platform (Boehme CC, 2010) (and more recently with a newer, apparently more sensitive version the Xpert Ultra not yet available for use). Xpert MTB/Rif reduces diagnostic delay and results in earlier TB treatment initiation (Theron G, 2014); TB preventive treatment guidelines for HIV-infected individuals have evolved to recommend long-term, more effective regimens (Samandari 2011, Martinson 2011), that when co-administered with antiretroviral therapy (ART), are safe and reduce mortality and TB disease (TEMPRANO ANRS 12136 Study Group 2015, Rangaka 2014). The CD4 threshold for initiating ART has been raised to 500 cells/mm3 and likely will be redundant when the test-and-treat strategy is implemented; and first line ART regimens have been simplified to single daily dosing with fixed-dose combination tablets. Moreover, children diagnosed with TB are increasingly being recognized as important sentinel cases for rapid identification of an infectious household TB case (Puryear,2013; Lala, 2014). Finally our data shows that HIV-seronegative household contacts in a high burden setting in the year after a household contact tracing intervention have annual TB incidence of 700/100,000 (van Schalkwyk, 2014) – suggesting preventive treatment against TB should be offered to HIV seronegative adults and older children in contact with a case, although this is not currently part of guidelines for preventive treatment in South Africa.

**We therefore hypothesise that a household intervention that actively includes these recent improvements will improve TB free survival** **and decrease the prevalence of new TB infections in children**.

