**Follow-up household visit (1week after baseline household visit)**
Xpert MTB results and results of laboratory HIV testing (and CD4 counts and HbA1C as appropriate) will be communicated to participants by study staff including registered nurses at a follow-up household visit approximately one-week after the baseline assessment is completed. Participants with microbiologically-confirmed tuberculosis or diagnosed with HIV will be supported to attend their nearest local primary care clinic to register for ongoing care and treatment.

Participants who are older than 5 years of age or test HIV-negative and whose sputum tests are negative for TB and whose tuberculin skin test is negative will be dispensed the first month of IPT by study nurse and then referred for ongoing preventive treatment at their local clinics with a clear referral letter that includes all results. Additionally all those participants who are less than 5 years of age or are HIV-positive and sputum tests are negative for TB will be dispensed the first month of isoniazid preventive therapy by study nurses, Linkage to care will be confirmed by collection of referral cards at study facilities by study staff. Home tracing to encourage re-entry to care will be undertaken on three occasions for participants who do not attend clinics within 2 weeks of referral.

Should any liquid TB culture be resulted positive after this visit, a visit will be made to the few anticipated households from where this result was taken to inform the patient and refer him/her for TB treatment.

| **Age of household member** | **HIV status** | **TST Required** | **Active TB disease** | **TB HH contact** | **IPT initiated** | **Study procedure** |
| --- | --- | --- | --- | --- | --- | --- |
| Child < 5 years | POSITIVE on ART or not | NO | NO | YES | YES | Initiate 1 month IPT |
| Child ≥5 years, adult or adolescent | POSITIVE on ART or not | NO | NO | YES | YES | Initiate 1 month IPT |
| Child < 5 years | NEG | NO | NO | YES | YES | Initiate 1 month IPT |
| Child ≥5 years, adult or adolescent | NEG | YES | NO | YES | YES | Initiate 1 month IPT |

Table 1. IPT initiation for household contacts without TB symptoms

*Final intervention household visit (3 months after baseline household visit)*

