**Data and Safety Monitoring Board**
We will establish a Data and Safety and Monitoring Board (DSMB) comprising of external experts, including a statistician experience in cluster-randomised controlled trials in sub-Saharan Africa, a clinical scientist experienced in TB management, and a lay member. The DSMB will meet four times: once prior to commencement of study activities; twice during the 15 month trial activity period, and once following completion of analysis. At each meeting, the DSMB will review a Trial progress report describing rates of recruitment and uptake of trial interventions, outcomes, and serious adverse events recorded. Because of the short duration of study activities, and the low potential for harm, interim analysis will not be performed.

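### Study nurses dispense isoniazid, but suspected reactions to it are not among the events to be recorded, so this harm cannot be reliably counted, attributed or promptly reported

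*Protocol*

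**What the plan says.** **Who receives the drug.** In the Protocol's section on the follow-up household visit, one group of contacts "will be dispensed the first month of IPT by study nurse and then referred for ongoing preventive treatment at their local clinics". Children under 5 and HIV-positive contacts with negative sputum "will be dispensed the first month of isoniazid preventive therapy by study nurses" as well. The Executive Summary lists as an intervention component "Preventive therapy for tuberculin skin test-positive, HIV-negative" and HIV-infected contacts without active disease. The Background argues for treating HIV-negative adults and older children, "although this is not currently part of guidelines for preventive treatment in South Africa".

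**What is recorded as a serious event.** The Adverse events section introduces its list with "Events deemed to be serious adverse events and systematically recorded and reported, and will include". Five items follow: misclassified or misread HIV or TB results, skin-test reactions, withdrawal because of stigma or a confidentiality breach, needlestick injuries, and violence or discrimination attributed to the study. Events judged serious go to all ethics boards within seven days and are reviewed by the DSMB. The section also promises case definitions and a reporting protocol.

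**Monitoring.** The DSMB section has the board meet four times, twice of these during trial activity. Each progress report covers recruitment, uptake, outcomes and recorded serious events. It adds: "Because of the short duration of study activities, and the low potential for harm, interim analysis will not be performed".

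**The concern.** The trial supplies one drug, and part of that supply is outside national guidelines by the protocol's own account. Control-arm contacts are referred for care under those guidelines, so this part of the exposure belongs to the intervention arm.

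The benefit of isoniazid is to be assessed. Its effectiveness in HIV-negative, skin-test-positive people is the first secondary objective, and TB incidence in intervention-arm members with and without it is the first exploratory outcome. The protocol has no matching measure of harm. At stake are participant safety and the trial's ability to weigh benefit against harm for a component that it may lead others to adopt.

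**Working it through.** The protocol states no figure on this point to reproduce. The check sets the passages side by side.

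**1. Suspected drug reaction.** Two listed items come close. One is "Adverse reaction to tuberculosis skin testing, such as ulceration, gangrene or loss of limb, disseminated infection, or death", which concerns the skin test only. The other is "Misclassification or misinterpretation of HIV or TB results leading to a participant starting treatment in error, or failing to start treating", which concerns treatment started by mistake and not a reaction to isoniazid that was correctly given. Neither covers a drug reaction. The Executive Summary says that the three-month visit assists people who have had problems with their treatment. The operative description of that visit covers people not accessing care, blood pressure and diabetes follow-up, social support and a TB symptom screen. It specifies no adverse-reaction question or record, and members absent on the day are not revisited.

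**2. Hospitalisation.** It is not in the serious-event list. It is recorded in both arms at the final outcome visit, from verbal report and patient-held records.

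**3. Death.** The list names it only as a consequence of skin testing. All-cause mortality, and TB- and HIV-related mortality, are between-arm secondary outcomes from baseline to month 15. Vital status and brief verbal autopsies are obtained at the final visit. Nothing links a death to isoniazid.

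**4. Timing.** Isoniazid is dispensed about 1 week after the baseline visit, for one month (about 4.3 weeks). The study's own supply therefore ends at about 1 + 4.3 = 5.3 weeks.
- Three-month visit: about 13 weeks, so 13 − 5.3 ≈ 8 weeks after that supply ends.
- Final visit: 15 months, about 65 weeks, so 65 − 5.3 ≈ 60 weeks after it ends. If the 15 months run from recruitment and the baseline visit falls up to 2 weeks later, the gap is about 58 weeks.

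A hospitalisation or death on the drug may thus first be recorded more than a year later, whereas a listed serious event goes to the ethics boards within seven days.

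**5. Scale, for orientation only.** The Sample size section gives 2,400 index cases and a mean household size of 5.5. Assuming equal allocation and full enrolment, there are 2,400 / 2 = 1,200 intervention households.
- If 5.5 counts contacts only: 1,200 × 5.5 = 6,600 people.
- If 5.5 includes the index case: 1,200 × 4.5 = 5,400 people.

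The protocol gives neither the share who would receive isoniazid nor a reaction rate, so no event count follows.

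**6. Who is exposed.** The follow-up visit text gives isoniazid to people whose skin test is negative (joining older age and HIV-negative status with an or). The Executive Summary specifies skin-test-positive people. The isoniazid table says that a skin test is required for HIV-negative people aged 5 or over, but not which result leads to treatment. These passages must be reconciled, because they define the group whose safety is to be followed.

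**The case against.** A reader might infer from the list that the trial cannot see isoniazid harm at all. The documents do not support that. Deaths and hospitalisations are recorded in both arms, mortality is compared between arms, in-patient days and outpatient visits are gathered by group for costing, and the three-month visit is meant to help people with treatment problems.

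A reader might also infer that death is missing from the list. It is named there, though only for the skin test.

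A third inference, that the DSMB would see no isoniazid harm, fails because its reports cover outcomes as well as serious events. Having no interim analysis is not the same as having no safety review.

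It is also tempting to multiply the number of contacts by an uptake and a reaction rate to obtain a count of missed events. Both rates would have to be invented.

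The best defence is that the list is not shown to be closed. Its introduction does not claim completeness, any event judged serious is reportable, and the promised case definitions and reporting protocol are not at hand and might name drug reactions. The study also dispenses only the first month, and for HIV-infected contacts the Executive Summary says that treatment follows current guidelines.

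These points narrow the concern but do not remove it. An open list gives field staff no instruction to ask about or record an isoniazid reaction. All five items are specific to this trial, so staff may well read them as the full set. What counts as a reportable safety event for a drug that the trial supplies belongs in the protocol and is not a detail for the analysis plan. The outcome data that reach the DSMB come mainly from month-15 visits.

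**Conclusion.** The concern holds in a limited form. The protocol does not name suspected isoniazid reactions among recorded events and gives no point at which to ask about them. Reactions that are neither fatal nor lead to admission have no specified systematic capture. Deaths and hospitalisations are captured, but mainly at month 15, outside serious-event reporting and without a link to the drug. Isoniazid harm therefore cannot be reliably counted, attributed or promptly reported.

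The gap touches some share of roughly 5,400 to 6,600 intervention-arm contacts, under the assumptions stated in the check. The number exposed and the number of reactions cannot be derived from the protocol. The conclusion depends on neither. It does assume that the promised case definitions do not already cover the point. If they do, the protocol should say so. This is an inexpensive improvement worth making, not a flaw that invalidates the trial.

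**What to change.** 1. In Adverse events, add to the list suspected reactions to study-dispensed isoniazid, and hospitalisation or death attributed to it. State whether this covers only the month that the study supplies or also the course that clinics continue.
2. In the description of the three-month visit, add a question on these events and a place to record the answer.
3. In the DSMB section, have these events tabulated in the progress report.
4. Separately, reconcile the follow-up visit text, the Executive Summary and the isoniazid table on which skin-test result leads to dispensing.

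Clinical handling of any reaction stays with the investigators.

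The cost is a few lines of protocol, one question at a visit already planned, and some additional seven-day reports to all ethics boards. The limits should be stated: the three-month data would come from the intervention arm only and from members present at that single visit, so they would be incomplete and without a comparator. The month-15 deaths and hospitalisations remain the only between-arm comparison.

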# Statistical Methods

### Sample size

Assuming a mean household size of 5.5 and household TB incidence the mean of that reported for each district, a sample size of 1,200 index cases in each district (2,400) in total, will provide 80% power at an alpha of 0.05 for the study to detect a 30% overall difference in TB free survival between groups with intracluster correlation coefficient of k=0.3. Routine TB data from both sites (Capricorn and Matlosana) suggest that they diagnose and treat at least double this number per annum.

### Statistical analysis

All statistical analysis will be conducted using R (The R Foundation for Statistical Computing, Vienna). All study data cleaning and analysis procedures will be fully documented in reproducible formats. Final, anonymised study datasets will be made available though an open access data repository based at the University of Liverpool UK to facilitate replication of analysis, and secondary analysis.

All analysis will be done on an intention to treat basis, with denominators comprising of households and household members randomly allocated to trial groups.

We will compare baseline household-, and index case-, and household members-level socio-demographic and clinical characteristics between allocated trial groups using absolute numbers and proportions for categorical variables, and means and standard errors, or medians and interqualitile ranges for continuous variables.

The following situations will be considered unbalance in baseline covariates between the two intervention groups:

- More than 5% difference between the two arms in: % male and proportion of index cases with bacteriologically-confirmed pulmonary tuberculosis.
- More than 5 years difference in mean age.
- More than 1 person difference in mean number of household members

If there is no unbalance in covariates, study conclusions will be based on the unadjusted analysis described below. Otherwise, study conclusions will be based on analysis adjusted for imbalanced covariates as described below.

The primary trial outcome (*TB free survival – both bacteriologically-confirmed TB, and all forms of TB - among household contacts identified at baseline between months 2 and 15*) will be estimated by a rate ratio and 95% confidence interval, with a 2-sided p-value<0.05 considered a statistically significant difference.

Because individuals will be clustered at the household level, we will use negative binomial generalised linear models with generalised estimating equations, accounting for clustered data with robust standard errors. We will assume an exchangeable correlation structure, whereby a correlation is taken to be constant between any two cluster members. As a sensitivity analysis, we will test the independent correlation structure. We will use person-years as an offset to the models to account for different amounts of time participants will be resident at the house. Where imbalance exists between trial groups (as defined above), analysis of outcomes will be adjusted for covariates that demonstrate important differences.

Analysis of secondary outcomes and exploratory outcomes will follow a similar approach, excepting where binomial outcomes are assessed (e.g. proportion of child household members with *MTB* infection, proportion of household members with undiagnosed or untreated HIV), in which case we will use log-binomial models, accounting for clustering with generalised estimating equations and robust standard errors.

The effectiveness of the intervention will be defined in terms of the primary outcome. A societal perspective will be taken for cost effectiveness: system and patient costs will be captured and analysed both jointly and separately to assess to whom benefits primarily accrue (see Economic Statistical Analysis Plan for full details).

6. Analysis populations

Outcomes will be assessed in two analysis populations: A) all household members who were listed at baseline for whom information is available at final study visit (“baseline cohort”); B) all household members for whom information is available at final study visit irrespective of presence at baseline (“final visit cohort”). Cohort A will be the primary analysis population. Results from cohort B will be used to investigate whether the effect of the intervention extends beyond those exposed to the intervention.

All analyses will be done on an intention-to-treat basis, i.e. data from household members included in populations A and B described above, will be included in the analysis, regardless of whether they underwent all intervention procedures in their trial arm. Household members will be defined as all individuals who either slept overnight at least once, or shared at least two meals in the same household as the index case in the 14 days prior to the index case’s diagnosis.

Additionally, for secondary outcome 1, the analysis population will be restricted to those individuals aged less than 14 years at the time of outcome assessment at 15 months and for secondary outcome 2, the analysis population will be restricted to those individuals with a bacteriologically-confirmed TB diagnosis during the follow-up period.7. Subgroup analysis

Subgroup analysis by study site (Capricorn District and Botshabelo District) will be conducted for all outcomes, in order to assess whether the effect of the intervention differs between a high (Botshabelo) and lower (Capricorn) TB burden setting.

8. Recruitment and trial profile

A trial profile figure will be produced illustrating the following, by trial arm:

• Number of index cases screened for enrolment

• Number of index cases excluded, with reasons

• Number of index cases enrolled and randomised

• Number of household members identified at baseline

• Of those household members identified at baseline, number whose vital status can be ascertained at 15 months

• Of those household members identified at baseline, number for whom data on TB diagnosis is available at 15 months

9. Baseline characteristics and descriptive analyses

Characteristics of index cases, their households and household members identified at baseline will be tabulated and summarised by trial arm. Absolute number and proportions will be used for categorical variables, and means and standard errors, or medians and interquartile ranges will be used for continuous variables.

Characteristics to be summarised will include

Index case characteristics:

• Age

• Sex

• Source of index case

• Vital status

• Presence and duration of TB symptoms

• Treatment received

• Laboratory confirmation of TB

• Co-morbidities including HIV

• Employment status

• Income

Household characteristics:

• Number of household members

• Number of rooms, windows, external doors

• Household crowding

• Household construction materials

Household member characteristics

• Relationship with recruited index case

• Airspace sharing with recruited index case

• Presence and duration of TB symptoms

• History of previous and current HIV treatment

• History of previous and current TB treatment

• Employment status

• Income

10. Statistical analysis of outcomes

Statistical analysis will be conducted using R (The R Foundation for Statistical Computing, Vienna, Austria) or Stata (StatCorp, College Station, Texas, USA). All analyses will employ statistical methods that allow for within-cluster (household) correlations. For all analyses, a 2-sided p-value<0.05 will be considered a statistically significant difference. No adjustment will be made for multiple testing.

Although baseline imbalance between the two intervention groups is unlikely due to the large sample size of this cluster randomised trial, the following situations will be considered as demonstrating imbalance in baseline covariates:

• More than 5% difference between the two arms in: % male and proportion of index cases with bacteriologically-confirmed pulmonary tuberculosis.

• More than 5 years difference in mean age.

• More than 1 person difference in mean number of household members

If there is no unbalance in covariates, study conclusions will be based on the unadjusted analysis described below. Otherwise, study conclusions will be based on analysis adjusted for imbalanced covariates as described below.

For the primary trial outcome (TB free survival), Poisson regression with random effects to account for clustering at the household level, will be used to estimate a rate ratio, 95% confidence interval and p-value for the effect of the intervention. To allow for the stratified randomisation by district, a fixed effect term for district will be included in the regression model. Where imbalance exists between trial groups (as defined above), these covariates will also be included in the regression model.

Analysis of secondary- and exploratory outcomes will follow a similar approach, except where binomial outcomes are assessed (e.g. proportion of child household members with MTB infection; proportion of household members with undiagnosed or untreated HIV), in which case we will use logistic regression with random effects to account for household clustering. For secondary outcome 5 (community HIV load), we will calculate this as the fraction of HIV-positive individuals with a measured viral load who have detectable viraemia multiplied by the number of individuals testing HIV-positive and divided by the total population with a measured HIV status.

Subgroup analysis will be done by examining stratum-specific (district-specific) rate ratios (or odds ratios for binary outcomes) and by fitting terms for the interaction between trial arm and district in random effects regression models.

Thematic content analysis with an inductive approach will be used to analyse transcripts for obvious and hidden content.

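### Cohort B contains all of cohort A, so a benefit in cohort B is not by itself evidence that the effect extends beyond those exposed

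*Protocol*

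**What the plan says.** The Analysis populations paragraph of the protocol's Statistical analysis section fixes two populations in which outcomes are assessed:

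- Cohort A, the primary population: "all household members who were listed at baseline for whom information is available at final study visit".
- Cohort B: "all household members for whom information is available at final study visit irrespective of presence at baseline".

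It then gives cohort B its purpose: "Results from cohort B will be used to investigate whether the effect of the intervention extends beyond those exposed to the intervention".

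The next paragraph names both populations and then defines a household member by contact before the index diagnosis: at least one night slept there, or having "shared at least two meals in the same household as the index case in the 14 days prior to the index case" was diagnosed. The same definition stands under Randomisation, allocation and blinding and under Study Definitions.

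The only effect modification examined is by district: "Subgroup analysis will be done by examining stratum-specific (district-specific) rate ratios", together with an arm-by-district interaction. The trial profile counts only members identified at baseline. Nothing estimates the arm effect in members not listed at baseline, and no contrast between A and B is specified.

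**The concern.** The question given to cohort B is about people other than those exposed. Everyone in cohort A is also in cohort B, so B is the listed members plus whoever else is found at the final visit. Its rate ratio is a weighted mixture of the direct effect and any effect in the others, and the listed members are likely to dominate the weights. A favourable result in B is therefore what one would expect from a direct effect alone.

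At stake is a secondary claim, but one that matters for policy in a trial of household transmission: that the benefit reaches people who were not there when the intervention was delivered. The protocol also sets a common threshold, "For all analyses, a 2-sided p-value<0.05 will be considered a statistically significant difference", with no adjustment for multiple testing, so a p-value below 0.05 in B would carry the label of significance.

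A second difficulty is separate from the first. Membership is tied to the 14 days before the index diagnosis. If that definition also governs B, people who joined the household later are not members and cannot enter it.

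**Working it through.** **The plan's own figure.** The protocol attaches no number to cohort B. The nearest figure is the Sample size statement that the trial "will provide 80% power at an alpha of 0.05 for the study to detect a 30% overall difference in TB free survival between groups". It is used below only to supply an effect size, read as a rate ratio of 0.70 in cohort A, and a reference level of power.

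**Step 1: expected rate ratio in B.** Let w be the share of B's expected control-arm events that comes from members not listed at baseline. Then

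RR(B) = (1 − w) × RR(A) + w × RR(unlisted).

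Take RR(A) = 0.70 and RR(unlisted) = 1.00, that is, no extension. The protocol gives no value for w, so 10%, 20% and 30% are assumptions.

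- w = 0.10: 0.90 × 0.70 + 0.10 × 1.00 = 0.73
- w = 0.20: 0.80 × 0.70 + 0.20 × 1.00 = 0.76
- w = 0.30: 0.70 × 0.70 + 0.30 × 1.00 = 0.79

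If unlisted members are instead 10% to 30% of the people in B, at the same rate but with half the person-time each, their event share is 0.5w / (1 − 0.5w). That is 5.3% to 17.6%, and RR(B) is 0.72 to 0.75. The smaller their contribution, the closer B sits to A.

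**Step 2: how often a test in B would be significant with no extension.** The inputs are 1,200 households per arm (from "a sample size of 1,200 index cases in each district (2,400) in total", assuming equal allocation, which is not stated), 5.5 members, 13 months, two-sided 5%, and k = 0.3 read as the between-household coefficient of variation. With λ0 and λ1 the arm rates and y the person-years per household,

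V = [(λ0 + λ1)/y + k²(λ0² + λ1²)] / (λ0 − λ1)², and power = Φ(√(1199/V) − 1.96).

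In cohort A, y = 5.5 × 13/12 = 5.96. In cohort B, y = 5.96/(1 − w) and λ1 = RR(B) × λ0.

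| Control rate per 100,000 person-years | Power in A | B, w = 10% | B, w = 20% | B, w = 30% |
|---|---|---|---|---|
| About 2,100 (set so that A has 80%) | 80% | 75% | 69% | 63% |
| 654 (mean of 937 and 371) | 35% | 31% | 28% | 25% |
| 528.5 (mean of 686 and 371) | 29% | 26% | 24% | 21% |

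Study setting gives three incidence figures for two named sites, so two possible means are shown. At either mean the stated 80% is not reproduced in cohort A. That is a separate matter and is not relied on here.

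A simulation at the first control rate (3,000 runs, gamma-Poisson households) gave 74%, 69% and 62% in B, with the estimated rate ratio below 1 in about 99% of runs. In unlisted members alone, where the truth was 1.00, the test rejected in 4% to 5%. With no effect in anyone (w = 20%), B rejected in about 5%.

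**Step 3: precision of the direct answer.** If the true rate ratio in unlisted members were also 0.70, power in them alone at the first control rate would be about 15%, 29% and 45% for w = 10%, 20% and 30%.

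**Step 4: the 14-day definition.** If it governs B, later arrivals are excluded, w falls towards zero and B nearly equals A. The figures in Steps 1 and 2 then do not apply to later arrivals. If it does not govern B, the paragraph needs to say so. The two difficulties are alternatives and cannot be added together.

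**The case against.** The strongest case against has five parts.

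- **No decision rule is stated.** A reader might infer that the protocol will declare extension whenever B shows a benefit, and so commits itself to a false conclusion. It does not say that. It says only that B's results will be used to investigate the question, and a contrast with A might be set out elsewhere. This stands. What remains is that the population chosen for the question does not isolate the people it concerns.
- **A and B together carry information.** With RR(A) at 0.70, B moves to 0.73 to 0.79 if there is no extension and stays at 0.70 if unlisted members benefit equally. This stands too, so it would be wrong to say that B is useless or can never separate the two effects. But the estimates overlap almost entirely and the shift is small, so the comparison is indirect and inefficient.
- **A significant false signal is not the expected result.** A reader might infer that B will show a significant benefit. The documents support this only for the expected rate ratio, and only if there is a direct effect. At the documented incidence the test in B would be significant in about 21% to 31% of trials.
- **The 14-day definition may be consistent with B.** B may be meant for people who met the definition but were missed in the index case's census. That reading is possible, but the text does not say so, and it would leave later arrivals out.
- **Cohort B is not primary.** Correct: it cannot alter the main conclusion.

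**Conclusion.** The concern holds in limited form. Cohort B as defined does not answer the question the protocol assigns to it, because it includes all of cohort A and nothing isolates members not listed at baseline. With a real direct effect and no extension, the expected rate ratio in B is still below 1: 0.73 to 0.79 given 0.70 in A, 1.00 in unlisted members, and an assumed 10% to 30% share of B's expected control-arm events. A benefit in B alone is therefore not evidence of extension. With no direct effect, B is not biased.

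The size rests on the assumed share and on reading the 30% difference as a rate ratio of 0.70; the direction rests on the two definitions alone. The conflict with the 14-day definition is a second, independent point. Neither touches cohort A or the primary analysis.

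**What to change.** In the Analysis populations paragraph:

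1. Answer the extension question in members with final-visit information who were not listed at baseline (B minus A), or by an arm-by-listed-at-baseline interaction.
2. Count their person-time from the date they joined the household.
3. State whether the 14-day member definition applies to them, and reconcile that paragraph with the definition of cohort B.
4. Keep full cohort B, if wanted, only as a whole-household effect, and describe it as such.
5. Label the analysis exploratory. The group is formed after randomisation, so its make-up may differ between arms, and the estimate will be imprecise (Step 3 of the working).

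The cost is a few sentences, one subset analysis and one data item. The final-visit tasks under Trial Procedures do not list a joining date for people not listed at baseline; the person-years offset only implies that residence time is known. The date should be added to what is recorded at that visit.
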